| 26 0/7 to 28 6/7 | 0.62                                     | 74.4%                                           | 25.6%                   |
| combined                               | 1.00                                     | 63.0%                                           | 37.0%                   |

We note that for sample size calculations we do not have numbers by site and thus assume a common effect, resulting in calculations that are based upon a randomized stratified design, which divides the sample among 2 strata at the assumed proportions observed in the VON data, assuming an uncorrected Cochran-Mantel-Haenszel test statistic with a two-sided 5% level test for *each* cohort, separately. Specifically, optimal target accrual for

the primary cohort of interest (cohort 1), summed across all strata, of 172 EPT infants in each intervention arm achieves approximately 80% power to test for a null odds ratio of 1.0 versus an alternative odds ratio of 0.5 (or a difference of 14% in rates). For cohort 2, optimal target accrual of 298 EPT infants in each intervention arm achieves approximately 80% power to test for a null odds ratio of 1.0 versus an alternative odds ratio of 0.55 (or a difference in rates of 12.5%). Shown in the table are estimated power calculations to assess each cohort assuming varying accrual proportions to the two cohorts and alternative odds ratios since accrual to each cohort cannot be controlled. The PASS 11 Power Analysis and Sample Size package was used to generate the sample size estimates.

| For total target accrual of N=940 EPT infants (N=N 1 +N 2 )
Assuming equal allocation (1:1) to intervention arms within each breathing cohort |                                                |                                               |                                        |          |          |
|------------------------------------------------------------------------------------------------------------------------------------------------------------------------|------------------------------------------------|-----------------------------------------------|----------------------------------------|----------|----------|

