If we set total target accrual to 940 eligible EPT infants and assume that at least 37% of accruals fall into cohort 1 then we will have approximately 80% power to detect an odds ratio of 0.5 for VentFirst compared to Standard for cohort 1 and we will have approximately 81% power to detect an odds ratio of 0.59 for VentFirst compared to Standard for cohort 2. Power increases for cohort 1 assessment as the proportion of accruals to that cohort increases and decreases in cohort 2 to as low as 72% for an odds ratio of 0.6. However, increasing our ability to assess the primary hypothesis at the cost of reducing the secondary is reasonable and still provides sufficient power to detect an odds ratio of 0.55. Given these conditions we will require accrual of at least 344 EPT infants to Cohort 1. If our assumptions on accrual proportions are incorrect and more than 65% of EPT infants are being accrued to cohort 2 then accrual to cohort 2 will be halted once 600 EPT infants are accrued.

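### Cohort 2 sizing sentence pairs about 80% power with odds ratio 0.55; the protocol's own table gives 89% there, and about 80% belongs to odds ratio 0.59

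*Protocol*

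**What the plan says.** All the statements are in Study Size Considerations, Section 7 of the protocol.

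- **Expected effect.** The section expects an odds ratio of 0.5 in cohort 1 and of either 0.59 or 0.55 in cohort 2.
- **Sizing sentence.** For cohort 2, a target of "298 EPT infants in each intervention arm achieves approximately 80% power" to test an odds ratio of 1.0 "versus an alternative odds ratio of 0.55 (or a difference in rates of 12.5" percent).
- **Power table, target row (344 and 596 infants).** Cohort 2 power is 96% at odds ratio 0.50, 89% at 0.55 and 81% at 0.59.
- **Paragraph after the table.** With a total of 940, the trial has "approximately 81% power to detect an odds ratio of 0.59 for VentFirst compared to Standard for cohort 2". If cohort 1 takes a larger share, power "decreases in cohort 2 to as low as 72% for an odds ratio of 0.6".

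The design behind these figures is given just before them: a test statistic described as "assuming an uncorrected Cochran-Mantel-Haenszel test statistic", "with a two-sided 5% level test for *each* cohort, separately", with a layout that "divides the sample among 2 strata at the assumed proportions observed in the VON data".

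**The concern.** The same 298 infants per arm and the same odds ratio of 0.55 have two different powers a few lines apart: about 80% in the sentence and 89% in the table. A gap of 9 points is not rounding. It is not an effect of reading the table from PDF either, because the later paragraph repeats the table's 81% at 0.59 in running prose.

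The expected cohort 2 effect is given as one of two odds ratios, so the sizing sentence is where the reader looks for the design alternative. It names one odds ratio with the power that belongs to the other. Hypothesis 2 has its own 5% test, and sizing text is often copied into reports. A later reader could wrongly believe that cohort 2 had only 80% power at 0.55.

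**Working it through.** **Inputs, all from Study Size Considerations**

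- Stratum shares: 0.38 (23 to 25 weeks) and 0.62 (26 to 28 weeks)
- Standard-arm failure rates: 55.1% and 25.6% (37.0% combined)
- Uncorrected Cochran-Mantel-Haenszel test, two-sided 5% (z = 1.96), 1:1 allocation, common odds ratio applied to failure

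**Formulas**

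In stratum s with m infants per arm (m = share × n), let p be the Standard failure rate and q the VentFirst rate, with q/(1−q) = OR × p/(1−p). Let p̄ = (p+q)/2. Then

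- D = Σ m(p−q)/2
- V0 = Σ (m/2) p̄(1−p̄) under the null
- V1 = Σ (m/4)[p(1−p) + q(1−q)] under the alternative
- Power = Φ[(D − 1.96√V0)/√V1]

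**Step 1: reproduce the cohort 1 figure (172 per arm, OR 0.5).** The VentFirst failure rates are 38.0% and 14.7%. D = 11.40, √V0 = 4.087, √V1 = 4.039, so z = 0.840 and power is 79.9%. The protocol says about 80%, so the method matches.

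**Step 2: cohort 2 at 298 per arm (m = 113.24 and 184.76)**

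| OR | VentFirst failure rates | D | √V0 | √V1 | z | Power | Protocol table |
|---|---|---|---|---|---|---|---|
| 0.55 | 40.3%, 15.9% | 17.33 | 5.415 | 5.366 | 1.252 | 89.5% | 89% |
| 0.59 | 42.0%, 16.9% | 15.48 | 5.440 | 5.402 | 0.892 | 81.4% | 81% |

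A simulation of the test with 200,000 replicates gave 89.6% and 81.4%.

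**Step 3: the rest of the table.** Powers at OR 0.50, 0.55 and 0.59, recalculated and then as printed:

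- 172 per arm: 79.9, 68.3, 58.0 (80, 68, 58)
- 298 per arm: 95.8, 89.5, 81.4 (96, 89, 81)
- 188 per arm: 83.4, 72.2, 61.9 (83, 72, 62)
- 282 per arm: 94.9, 87.8, 79.2 (95, 88, 79)
- 235 per arm: 90.6, 81.3, 71.6 (91, 81, 72)

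Every printed cell agrees within one point. Only the sizing sentence does not.

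**Step 4: can another reading give 80% at OR 0.55 with 298 per arm?** At the stated two-sided 5% level:

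- continuity-corrected test: 87.7%
- unstratified test at 37.0%: 91.7%
- odds ratio applied to success instead of failure: 93.0%

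Halving alpha to 0.025 gives 83.3%. It takes an alpha of about 0.017 to bring power down to 79.2%, and the protocol states no such level. With 298 per arm and the stated design, 80% power falls at an odds ratio of about 0.596.

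**Step 5: the 72% figure.** With 235 per arm (the 470 and 470 row), power is 71.6% at OR 0.59 and 68.9% at OR 0.60. The 72% in the paragraph is the table's value for 0.59.

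**The case against.** The strongest reply is that nothing operative rests on the sentence. The paragraph after the table justifies the total of 940 with figures that are correct: about 80% at 0.5 in cohort 1 and 81% at 0.59 in cohort 2. The sentence errs on the cautious side. The table's footnote also says that the hypothesised alternatives are marked in bold. That marking cannot be seen in the text used here, so the formatted protocol may show the cohort 2 alternative directly. All of this stands, and it limits the point to a wrong sentence.

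It also rules out four stronger readings that a reader might be tempted by:

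- *The totals of 596 and 940 lack a valid basis.* They do not, because the later paragraph supplies one.
- *Cohort 2 over-enrols.* About 228 per arm would give 80% at 0.55, and 596 − 2 × 228 = 140. That counts as excess only if 0.55 were the sole alternative. The protocol names 0.59 as well and uses it to support the total; 80% power at 0.59 needs about 288 per arm.
- *A null result in cohort 2 could not be interpreted.* Analyses of the Primary Endpoint provides a 95% confidence interval for the relative risk within each cohort, which serves that purpose.
- *The differences of 14, 12.5 and 11% are wrong.* They are the odds ratios applied to the stated combined rate of 37.0%, which gives 14.3, 12.6 and 11.3 points. They are fair descriptive labels and do not enter the power figures.

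The 0.6 in the later paragraph may be loose rounding of 0.59. It is worth correcting only because the rounded value corresponds to a different power.

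**Conclusion.** The sizing sentence for cohort 2 is wrong as written and contradicts both the table and the paragraph after it. At 298 per arm, power is 89.5% at odds ratio 0.55, not about 80%; about 80% belongs to 0.59 (81.4%). The sentence understates power by about 9 points, so cohort 2 is not underpowered, and the targets of 596 and 940 do not change. The odds ratio of 0.6 paired with 72% is a secondary slip worth about 3 points (68.9% against 71.6%).

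The result rests on the protocol's own stratum shares, failure rates, test and alpha, with a common odds ratio on failure. Those inputs reproduce every cell of its table. The size of the point is that of a text correction.

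**What to change.** In Study Size Considerations, correct the cohort 2 sizing sentence in one of two ways:

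- about 81% power at an odds ratio of 0.59 (11%), which agrees with the paragraph after the table; or
- about 89% power at an odds ratio of 0.55 (12.5%).

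Both are arithmetically right. The sponsor should choose the one that reflects the intended design and use the same cohort 2 alternative throughout the section. In the paragraph after the table, change the odds ratio attached to 72% from 0.6 to 0.59 (power at 0.60 with 235 per arm is about 69%).

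The cost is two edits to the text. The number of infants, the alpha and the analysis do not change.

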## Interim Analysis and Stopping Guidelines

This study is designed using one interim look for efficacy of the primary outcome and one final look for a total of 2 planned analyses of the primary outcome in cohort 1. There are no interim analysis plans for cohort 2 or for futility; however, the proposed timeline can be modified based upon input from the DSMC. The guidelines serve as a trigger for consultation with the DSMC for additional review and are not formal “stopping rules” that would mandate automatic closure of study accrual. Adverse events and other safety endpoints will be monitored regularly and reported at each meeting of the DSMC.

## Guidelines for Safety Monitoring

The DSMC will receive periodic safety reports of all adverse events and serious adverse events on the timeline specified in the DSMC charter. Monitoring of high grade (grade III-IV) IVH will be conducted monthly by the study PIs, and if rates approach near pre-set thresholds, the DSMC chair will be notified. The stopping guidelines serve as a trigger for

consultation with the DSMC for additional review. Statistical monitoring bounds for safety will be limited to the cumulative incidence of high grade IVH which will be monitored separately for each treatment arm within each cohort. Results from VON indicate high grade IVH event rate of 9.6%, 13.0% and 18.9% for the mean, 75th and 90th percentile, respectively. The upper boundary of a sequential probability ratio test (SPRT) based upon a binomial test of proportions of babies with high grade IVH will be used for monitoring to protect against excessive high grade rates. The stopping boundary are for a SPRT contrasting an acceptable rate of 9.6% versus a high rate of 18.9% of high grade IVH rate, with nominal type I and II errors of 5% and 20%, respectively. The slope of the parallel lines for monitoring is 0.1381 and the intercept is 3.5277. If a stopping bound is crossed then accrual to the study will be suspended until the DSMC can review the data, and determine if the study should continue, be amended or be closed to further accrual.

### **Demographic and Baseline Characteristics**

Demographic and baseline characteristics will be summarized for all eligible mothers and EPT infants registered to the study by cohort and intervention arm.

### **Analysis Plan**

#### **Analysis Populations:**

##### **Intent-to-treat (ITT)**

The primary analysis will be based on all randomized eligible EPT infants, and will be based on the arm they were randomized to regardless of intervention received (intent-to-treat).

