#### **Exclusion Criteria (All exclusion criteria MUST NOT be present)**

- [1] Life threatening condition of fetus (including but not limited to: severe hydrops, lethal chromosomal abnormality, severe congenital malformation)
- [2] Suspected severe fetal anemia
- [3] Monochorionic twins
- [4] Multiple gestation greater than twins
- [5] Decision made for comfort care only
- [6] Medical emergency necessitating emergency delivery (e.g., complete placental abruption)
- [7] Obstetrician or Neonatology concerns for inappropriateness of the study intervention based on other maternal or fetal factors (must specify reason on the screening log)

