**Discontinuation/Withdrawal from Study**

Participants may be withdrawn or be discontinued from the study at any time for any of the following reasons:

- Mother withdraws consent
- Obstetrician or neonatology physician determines that a maternal or fetal condition precludes the study intervention
- Sponsor PI closes the study
- The DSMC or a local IRB deems it necessary

If a mother withdraws consent prior to birth, the study intervention will not be performed and the mother's prenatal data and the reason for withdrawal of consent will be documented in the study database.

If maternal consent is withdrawn at any point after the study intervention, all data obtained prior to the time of consent withdrawal will be used for data analysis, but data will not be collected after withdrawal.

All participants that withdraw from the study will receive standard treatment.

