##### **Per Protocol population**

A per protocol population will be used for secondary sensitivity analyses of the primary and secondary outcomes and will include all randomized EPT infants that do not have protocol deviations: 1) Eligibility violation 2) Intervention non-adherence 3) Intervention crossover 4) Missing primary outcome information.

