### **Handling protocol deviations or losses to follow-up**

All randomized on-study EPT infants will be assessed for study endpoints even if there are major protocol deviations or they are deemed ineligible. For the primary outcome, any infant that dies at <7 days will be considered an intervention failure. For any surviving infant who has not had a HUS day 7-10 this will be a protocol deviation and there will be a reminder and an

extension to day 14. If a surviving infant has no HUS from day 7-14 this will be a protocol violation and the next available HUS after day 14 will be used for determination of the primary outcome. For secondary outcomes it is highly unlikely that data will be unavailable in the medical records of the delivery hospital until discharge home or 36 weeks PMA (whichever comes first). For infants who are transferred, study coordinators will contact the transfer hospital for secondary outcomes to 36 weeks PMA, with maternal consent. In the rare instances where there is insufficient information, secondary outcomes will be assessed based upon the latest information after consensus review by PIs or the DSMC, as described in the MOP.

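### The primary intent-to-treat set is limited to eligible infants, while the deviations rule keeps ineligible ones; the two conflict and leave room for an arm-aware exclusion

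*Protocol*

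**What the plan says.** The Synopsis (Statistical methods, Efficacy) and Section 7, Intent-to-treat (ITT), use the same definition: "The primary analysis will be based on all randomized eligible EPT infants", by the arm assigned and whatever intervention was received.

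Section 7, Handling protocol deviations or losses to follow-up, says: "All randomized on-study EPT infants will be assessed for study endpoints even if there are major protocol deviations or they are deemed ineligible". It then goes straight on to the rules for scoring the primary outcome. Section 4, Subject Status Definitions, treats a dyad as on-study from randomisation unless consent is withdrawn, so this rule covers nearly everyone randomised.

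On timing, Section 4 (Screening, Randomization) requires eligibility to be confirmed before randomisation. Footnote 1 to the Schedule of Events (Table 1) asks only that it be confirmed before the study intervention. The inclusion criterion is gestation at delivery. The exclusion criteria include emergency delivery and "Obstetrician or Neonatology concerns for inappropriateness of the study intervention based on other maternal or fetal factors". The server displays the arm to staff at randomisation, preferably within an hour of the expected delivery.

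**The concern.** An infant found ineligible after randomisation is outside the primary set under one rule and assessed for endpoints under the other. A later analyst could cite either rule.

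This matters because eligibility is not closed at randomisation. An emergency, or a clinician's concern about the study intervention, can arise between randomisation and birth, when the team knows the arm. If it is recorded as a deviation, the infant stays in the intent-to-treat comparison. If it is recorded as a failed exclusion criterion, the infant is not an eligible one and could be dropped. A concern about the study intervention is more naturally raised about VentFirst than about routine care, and such infants may be at higher risk. Removing them from one arm only would favour that arm. Blinded reading of the head ultrasounds cannot repair a set that has already been selected.

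**Working it through.** **The passages side by side**

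| Place | Infants covered |
|---|---|
| Synopsis; Section 7, ITT | randomised and eligible |
| Section 7, Handling protocol deviations | randomised and on-study, ineligible infants included |
| Section 7, Safety population | all randomised |
| Section 7, Per Protocol population | all randomised, less listed deviations |

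The first two rows disagree. The safety definition omits *eligible*, so the word in the ITT definition reads as a restriction. Reading *assessed* in the deviations rule as data collection only would leave ineligible infants outside an analysis called intent-to-treat.

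**The plan's own power figure.** Inputs from Section 7, Study Size Considerations: stratum weights 0.38 and 0.62, Standard failure rates 55.1% and 25.6%, odds ratio 0.5, 344 infants allocated 1:1, two-sided 5% Cochran-Mantel-Haenszel (CMH) test.
- VentFirst failure rates: 0.380 and 0.147.
- Weights h = n/4: 32.68 and 53.32.
- Numerator Σh(p−q) = 32.68×0.171 + 53.32×0.109 ≈ 11.40.
- Standard deviation: 4.09 under the null, 4.04 under the alternative.
- Power = Φ((11.40 − 1.96×4.09)/4.04) ≈ 79.9%. The stated 80% is reproduced.

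**Exclusions balanced between arms and unrelated to outcome.** Power falls to 79.1%, 77.9% and 75.6% with 2%, 5% and 10% removed. There is no bias.

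**Exclusions from VentFirst only.** The documents give no rate of later ineligibility, so the fraction removed (f) and the failure rate among those removed (q) are assumed. With no true effect:
- remaining failure rate = (0.37 − f·q)/(1 − f)
- SE = √(2×0.37×0.63/172) = 0.0521
- type I error = Φ(−1.96 + z) + Φ(−1.96 − z), where z = shift/SE

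At f = 5%, q = 65%: (0.37 − 0.0325)/0.95 = 0.3553; shift 1.5 points; z = 0.283; type I error 5.9%.

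At f = 10%, q = 65%: (0.37 − 0.065)/0.90 = 0.3389; shift 3.1 points; z = 0.598; type I error 9.2% (9.0% if the SE uses the reduced arm size).

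Over q = 55% to 80%, with the reduced arm size:

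| Removed | Cohort 1 (172 per arm) | Cohort 2 (298 per arm) |
|---|---|---|
| 2% | 5.1-5.3% | 5.1-5.6% |
| 5% | 5.4-7.2% | 5.6-8.8% |
| 10% | 6.6-14.7% | 7.8-22.1% |

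At q = 37% the shift is zero and type I error stays at 5.0%.

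**Effect of stratification.** The planned test is stratified by gestational age. Suppose all exclusions come from the 23-25 week stratum, where failure is already 55.1%. In cohort 1 with q = 65%:
- f = 5% removes 0.05/0.38 = 13.2% of that stratum. Failure there falls to 53.6%. The CMH-weighted shift is 30.38×0.0150/(30.38 + 53.32) ≈ 0.5 points, and type I error is 5.1%.
- f = 10% removes 26.3%. Failure there falls to 51.6%. The weighted shift is 27.73×0.0354/(27.73 + 53.32) ≈ 1.2 points, and type I error is about 5.6-5.7%.

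At q = 55.1% the shift is zero. If exclusions are spread across the strata in proportion, stratification gives no such protection.

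**The case against.** The strongest reply is that eligibility in this protocol is a screening status. It must be confirmed before randomisation and reconfirmed at readmission, and the reason for a clinician's concern goes on the screening log. Later problems have their own routes. In an unanticipated emergency the clinician may deviate from or end the protocol procedures (Section 4, Post-Delivery Instructions), and Section 10, Emergency Modifications, calls for a deviation or violation form. The ITT definition keeps such infants in their assigned arm. No text provides for reclassifying a randomised infant as ineligible because of its arm. All of this stands, and it limits the likely number of cases. It does not remove the conflict, because no sentence confines *eligible* to what was known before randomisation, or says who judges later ineligibility and whether that person is blind to arm.

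Three stronger inferences are tempting but unsupported.

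- *The per-protocol list proves that the ITT set keeps ineligible infants.* It does not. That definition starts from all randomised infants, so its list ("1) Eligibility violation 2) Intervention non-adherence 3) Intervention crossover 4) Missing primary outcome information") would be needed however ITT is defined.
- *The withdrawal ground ("Obstetrician or neonatology physician determines that a maternal or fetal condition precludes the study intervention") removes infants from analysis.* The status definitions take a dyad off on-study status only when consent is withdrawn, and a physician's decision is not that.
- *Gestation at delivery gives an arm-aware route.* It is settled after randomisation, but it is not a judgement about the assigned intervention.

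**Conclusion.** The inconsistency is certain from the text: the primary set is defined in two incompatible ways. The bias is only possible. A reader might infer that the result will be tilted toward VentFirst, but the documents do not show that such exclusions will occur, that they would be one-sided, or that the infants removed would be at higher risk.

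If all three held, a 2% removal would be negligible. A removal of 5-10% at 65% failure would give a spurious benefit of 1.5 to 3.1 points in cohort 1 on the unstratified test, or 0.5 to 1.2 points if the exclusions sit in the 23-25 week stratum and the planned stratified test is used. The plan targets a difference of about 14 points. The point is worth correcting because it defines the confirmatory comparison and costs almost nothing to settle; it does not show that the trial's conclusion is unsound.

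**What to change.** Delete *eligible* from the definition in the Synopsis and in Section 7, Intent-to-treat (ITT). Define the primary set as every infant born to a randomised mother, analysed by assigned arm, in line with the deviations section. If any exclusion is kept, limit it to objective facts that the assigned arm cannot affect, judged blind to arm and outcome. Leave eligibility violations as a per-protocol exclusion, where they already stand.

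The cost is a wording change in two places and slight dilution from a few off-criteria infants. Planned power at 172 per arm stays at about 80%. The 940 target is stated in eligible infants (Accrual; Study Size Considerations), and that wording should be aligned.
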